### Primary outcome measures

#### Safety

To evaluate the safety of administered tolDC, occurrence of AE will be recorded using clinical outcome measures, that is, physical (skin, pain and adenopathies) and neurological examination (relapses and worsening disability) and non-clinical outcome measures, that is, brain MRI, biochemical and haematological safety. The frequent MRI monitoring will allow us to monitor the safety of tolDC in MS patients objectively by measuring T1-enhancing lesions and new and/or enlarging T2 lesions. In this way, unexpected disease activity can be detected timely. The severity of AE will be defined according to the WHO toxicity grading scale. The relationship of an AE to the investigational product will be determined by the neurologists and the independent DSMB on the basis of their clinical judgement.

A proportion of the patients may experience MS relapses during the study. A relapse is defined as a new or worsening neurological symptom that occurs in the absence of fever or infection, occurs at least 30 days following the onset of a previous relapse, persists for at least 24 hours and includes an increase in Expanded Disability Status Scale (EDSS) score^42^ from the previous assessment matching one of the following: (i) an increase of ≥1 on the total scale score; or (ii) an increase of ≥2 points on one of the appropriate Functional System Scores (FSS) or (iii) an increase of >1 point on two or more of the appropriate FSS. Patients will be instructed to notify their neurologist as soon as possible but within 72 hours the latest and will be examined within 7 days of onset of the symptoms. In case of an MS relapse, a course of high-dose steroids can be administered at the discretion of the treating neurologist.

Study treatment must be discontinued for a given patient if the investigator determines that continuing would result in a significant risk for that patient. In case of terminating the study treatment, patients will still be monitored for safety issues for the duration of the study.

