### Study population

#### Eligibility and enrolment

Patients with active relapsing-remitting and active progressive MS, diagnosed according to most recent McDonald criteria,^39 40^ and who are not eligible for or do not want to be treated with currently available DMT, will be recruited. Patients are included after written informed consent and enrolled in the study when the inclusion and exclusion criteria are met (table 2).

**Table 2 T2:** Inclusion and exclusion criteria. All the inclusion criteria must be fulfilled. The presence of any of the exclusion criteria shall exclude the patient

Inclusion criteria	Exclusion criteria
MS according to most recent McDonald criteria	Previous use of immunosuppressive or cytostatic treatment, including mitoxantrone, cladribine, alemtuzumab or bone marrow transplantation or stem cell transplantation at any time prior to enrolment
Age 18–60 years	Treatment with fingolimod or natalizumab or dimethylfumarate in the past 12 weeks or teriflunomide within the past 15 weeks or ocrelizumab/rituximab within the past 6 months prior to the first administration
EDSS of 0–6.5 inclusive	Pregnancy or planning pregnancy in the next 12 months and breast feeding
First signs or symptoms at least 3 months prior to enrolment in the study	Drug or alcohol abuse
Active MS (relapsing and/or progressive): one relapse in the past year and/or at least one enhancing lesion on brain MRI in the past year; at least one new or enlarging T2 lesion in comparison with a reference scan from maximum 1 year before	Inability to undergo MRI assessments
Normal peripheral B-cell count after treatment with ocrelizumab	
No evidence of relapse for at least 30 days prior to start of screening and throughout during the screening phase	History of or actual signs of immunodeficiency or malignancies
Positive T cell reactivity response to a mix of seven myelin-derived peptides	Concurrent clinically relevant cardiac, immunological, pulmonary, neurological, renal or other major disease
Able to sign informed consent and comply with the protocol assessments	Active or chronic infection (hepatitis B or C, HIV, syphilis or tuberculosis)
No wish to be treated with currently available DMT	Splenectomy
Appropriate venous access and *adequate cervical lymph nodes on ultrasound mapping	

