**Figure 1 F1:**
[figure not shown]
Study design. Treatment will start at V_1_, approximately 4 weeks after the leukapheresis. Patients will receive additionalinjections on week +2 (V_2_), week +4 (V_3_), week +6 (V_4_), week +10 (V_5_) and week +14 (V_6_). Patients will have follow up visits one month, and 3, 6 and 12 months following the last study treatment.

**Table 4 T4:** Study calendar. The different visits, examinations, tests and the tolDC administration are detailed on the tabular study schedule overview.

	Screening		Treatment period							Safety follow-up			
	Ts	Baseline (T0)	V1	V1 +1 day	V2	V3	V4	V5	V6	F1	F3	F6	F12
Informed consent	·												
Inclusion and exclusion criteria	·												
IFN-γ EliSPOT (T cell reactivity assay)	·		·				·+1w		·+1w		·		
Leukapheresis		·											
TolDC preparation		·											
TolDC treatment			·		·	·	·	·	·				
Patient evaluation:													
Vital signs (HR, BP, …)	·	·	·		·	·	·	·	·	·	·	·	·
ECG	·	·	·		·	·	·	·	·	·	·	·	·
Blood analysis for safety (1×5 mL EDTA tube and 2×10 mL serum tubes)	·	·	·		·	·	·	·	·	·	·	·	·
Urine pregnancy test	·	·	·		·	·	·	·	·	·	·	·	·
Full neurological examination (EDSS, 9-HPT, T25FW, SDMT, MSQOL-54)	·		·										
Pain score after treatment injection			·		·	·	·	·	·				
MRI	·	·	·		·		·+1w	·+1w	·+1w		·	·	·
Immunomonitoring (10×10 mL heparin tubes+1 serum tube)			·				·+1w		·+1w		·		
Biobanking for follow-up immunomonitoring													
(Serious) Adverse events and concomitant medication	Continuous												

BP, Blood Pressure; ECG, Electrocardiogram; EDSS, Expanded Disability Status Scale; 9-HPT, 9 Hole Peg Test; MRI, Magnetic Resonance Imaging; MSQOL-54, Multiple Sclerosis Quality of Life-54; SDMT, Symbol Digit Modalities Test; T25FW, Timed 25 Foot Walk; tolDC, tolerogenic dendritic cells.

In Belgium (MS-tolDC), tolDC vaccination occurs through intradermal injection at five alternating sites (100 µL/site) in the posterior neck region to ensure lymphatic drainage to superficial and deep cervical lymph nodes (5–10 cm from the cervical lymph nodes). In addition, in Spain (TOLERVIT-MS), an expert physician will inject tolDC directly in the cervical lymph nodes under echographic guidance. If the patient’s anatomical conditions do not allow it (eg, small lymph nodes), the vaccine will be distributed in more nodes (max. 500 µL/node).

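### The relapse definition allows a score taken during a relapse to be the reference, so a repeat or stepwise relapse can go uncounted

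*Protocol article*

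**What the plan says.** The protocol article, under Primary outcome measures, Safety, gives a working definition of a relapse. The symptom must be new or worse, without fever or infection, and must last at least 24 hours. It counts only if it "occurs at least 30 days following the onset of a previous relapse" and if it "includes an increase in Expanded Disability Status Scale (EDSS) score^42^ from the previous assessment matching one of the following". The three limbs are:

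- (i) a rise of 1 or more in total EDSS;
- (ii) a rise of 2 or more on a single functional system score;
- (iii) "an increase of >1 point on two or more of the appropriate FSS".

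The same paragraph says that a patient with symptoms "will be examined within 7 days of onset of the symptoms". No sentence there or elsewhere in the article says that the previous assessment must be stable, relapse-free or a minimum time earlier.

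Relapses are listed with worsening disability among the neurological findings that feed the primary safety outcome. Table 2 requires that patients have had no relapse for 30 days before screening and have none during it, so every patient starts with a relapse-free score.

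**The concern.** All three limbs depend on the most recent examination, whatever state the patient was in at the time. The protocol itself produces an examination during each relapse, because it calls patients in soon after onset. Unless a recovery examination follows, that raised score becomes the reference for the next episode. The 30-day clause separates the onsets of two relapses but does nothing to protect the reference score.

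Two kinds of event are exposed. One is a second relapse that does not exceed the score at the first by the threshold. The other is a relapse that builds up across two examinations, each step below the threshold.

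Both concern patients with recurrent or slowly evolving activity, which matters in a trial that watches for unexpected disease activity. Cohorts have 3 to 5 patients, and the article intends to compare results between the two trials, so both sites need to count relapses in the same way.

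**Working it through.** The plan states no figure to reproduce, so the check applies limb (i) to assumed EDSS paths under two references. The EDSS values and days are assumptions chosen to test the rule, not trial data.

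**Inputs from the Safety section:** a threshold of 1 point on total EDSS; examination within 7 days of onset; at least 30 days between onsets.

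**Rules compared**
- As written: change = score now − score at the previous assessment; counted if the change is at least 1.
- Re-anchored: change = score now − last score outside a relapse; counted if the change is at least 1.

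| Assumed path (day: EDSS) | As written, last examination | Re-anchored, last examination |
|---|---|---|
| A. Repeat relapse: 0: 2.0; 33: 3.5; 73: 3.5 | 3.5 − 3.5 = 0, not counted | 3.5 − 2.0 = +1.5, counted |
| B. Stepwise relapse: 0: 2.0; 33: 2.5; 44: 3.0 | 3.0 − 2.5 = +0.5, not counted | 3.0 − 2.0 = +1.0, counted |
| C. Larger second relapse: 0: 2.0; 33: 3.5; 73: 4.5 | 4.5 − 3.5 = +1.0, counted | 4.5 − 2.0 = +2.5, counted |
| D. Repeat with recovery examination: 0: 2.0; 33: 3.5; 60: 2.0; 73: 3.5 | 3.5 − 2.0 = +1.5, counted | 3.5 − 2.0 = +1.5, counted |
| E. Slow rise examined once: 0: 2.0; 44: 3.0 | 3.0 − 2.0 = +1.0, counted | 3.0 − 2.0 = +1.0, counted |

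In path A the first relapse is counted under both rules (3.5 − 2.0 = +1.5). In path B the first step is 2.5 − 2.0 = +0.5 under both, so as written the episode is never counted.

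**Does path A satisfy the 30-day clause?** Each examination falls 0 to 7 days after onset. The first onset is therefore on days 26 to 33 and the second on days 66 to 73. The gap is at least 66 − 33 = 33 days and at most 73 − 26 = 47 days. The clause is met, so only the reference score stops the second relapse from counting.

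**Can this arise on the visit schedule?**
- Table 4, as it reads in the text available, marks the full neurological examination only at screening and V1. Taken at face value, no scheduled EDSS would reset the reference from V1 to the last visit, 14 + 52 = 66 weeks later. The table may be incomplete in that text: the Analysis section calls EDSS repeatedly measured, and Clinical evaluation uses 3-month sustained EDSS change. The point does not rest on it.
- If EDSS is done at every visit, follow-up is at 1, 3, 6 and 12 months after the last treatment. The gaps are 3 − 1 = 2, 6 − 3 = 3 and 12 − 6 = 6 months. Each exceeds 30 days, so two countable onsets can fall within one gap with no scheduled examination between them.
- More frequent visits make path A less likely but path B more likely. V1 to V4 are two weeks apart, so a treatment visit could supply the intermediate sub-threshold score.

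**Limit of the check.** It uses total EDSS only. A second relapse in a different functional system could still qualify under limb (ii) or (iii). In path A the functional system limbs also fail if the second relapse returns to the same level in the same system.

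**The case against.** The strongest reply is that this is a wording point with little safety consequence. The primary safety objective is the occurrence and severity of adverse events, not a count of protocol-defined relapses. Adverse events are recorded continuously, neurological worsening is captured whatever its label, and repeated MRI is the stated means of detecting unexpected activity. Escalation rests on dose-limiting toxicities and on the judgement of the investigators and the DSMB. The Analysis section names no relapse-rate analysis. Progression is measured from baseline and so escapes the moving reference. One could also read the previous assessment as the one before the episode began.

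Much of this stands and limits the consequence. It does not remove the defect. The literal text ties the rule to the last examination, and the favourable reading appears nowhere. The definition is stated in full rather than left to another document.

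It is also fair to say that the two failures need particular circumstances. A repeat relapse is lost only without a recovery examination in between and only if it is not clearly worse than the first. A stepwise relapse is lost only if a second examination falls within the same episode, while the protocol calls for one. Both conditions belong in the conclusion.

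**Conclusion.** The point holds in conditional form: relapses can go uncounted under the literal rule, not that they always do. Two of five assumed paths lose an event and three do not. The conclusion assumes that the rule is applied as written and that no functional system limb is met independently. It also assumes no recovery examination between two relapses, or an intermediate sub-threshold examination within one. How often this would happen cannot be estimated from the document. The size of the problem is the relapse label and the event count.

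Three stronger readings are not supported:

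- **Safety events are lost altogether.** They are not; a symptomatic episode can still be recorded as an adverse event, and MRI is repeated.
- **One missed relapse equals 20% to 33% of a cohort** (1/5 to 1/3). In the repeat-relapse path the patient already counts as relapsing, so the share of patients with a relapse does not change. A stepwise relapse that was a patient's only one could leave that patient unlabelled, but the document gives no basis for a cohort-level figure.
- **Slow progression is filed as relapse because progressive patients are eligible.** The definition also needs a new or worsening symptom, and patients must report it and be examined within days of onset. This worry is also no argument for re-anchoring, which can only keep the reference or move it to an older score.

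**What to change.** In the relapse definition, replace the reference to the previous assessment with: *from the last assessment before onset of the new symptoms that was not made during a relapse (at least 30 days after onset of any earlier relapse)*. Make clear that an assessment preceding the earlier relapse also qualifies; otherwise path A would have no valid reference. Apply the wording to the total EDSS limb and both functional system limbs, identically in MS-tolDC and TOLERVIT-MS.

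This changes one sentence of an outcome definition. It needs no extra visit or procedure and does not touch treatment. The downside is that the reference will sometimes be an older score, so some gradual change since then can count towards the threshold.

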### Secondary outcome measures

#### Clinical evaluation

The following clinical and laboratory assessments will be performed during a complete physical examination: vital signs, ECG, routine blood and urine samples, urine pregnancy test in female patients of reproductive potential and serological screening tests, according to the study schedule (figure 1 and table 4). Concurrent drug use or new AE will be reviewed and recorded.

EDSS is based on a standardised neurological examination and measures impairments in eight functional systems, including vision, brainstem, pyramidal, cerebellar, sensory, bowel and bladder, mental (cerebral) and ambulation. It has been used for over 20 years as a clinical outcome measure of MS disease progression and consists of a 10-point scale of disease severity ranging from 0, that is, no disability, to 10, that is, death from MS.^42^ All neurologists involved in patient evaluation will be EDSS training certified.

EDSS will be supplemented by three well-known, quantitative, continuous tests that evaluate ambulation (walking speed by the timed 25 foot walk test or T25FW, arm dexterity and function by the 9 Hole Peg Test or 9-HPT, and cognition by the Symbol Digit Modalities Test or SDMT).

The effect on disability progression will be characterised by reporting the proportion of patients who are free from disease progression. For this, disability will be assessed based on a sustained clinically relevant change seen in any one of the disability assessments: EDSS, T25FW, SDMT or the 9-HTP. Disease progression is defined by: 3-month sustained increase from baseline in the EDSS score (1 point in patients with baseline EDSS score 0 to 5.0; 0.5 point in patients with baseline EDSS score of 5.5–6.5) or 3-month sustained increase of at least 20% from baseline in the time taken to complete the T25FW or 3-month sustained increase of at least 20% from baseline in the time taken to complete the 9-HPT. Percent change from baseline after treatment in SDMT score will also be recorded.

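### With whole-point functional system scores, the third limb of the relapse definition adds nothing to the second, so 1-point rises in two or more systems count only if the total EDSS also rises by at least 1

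*Protocol article*

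**What the plan says.** Under Primary outcome measures, Safety, the protocol article lists "neurological examination (relapses and worsening disability") among the clinical measures used to record adverse events. It then defines a relapse. Besides conditions on symptoms, duration, spacing and absence of fever or infection, the event must show an EDSS increase "from the previous assessment matching one of the following":

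- limb (i): "i) an increase of ≥1 on the total scale score"
- limb (ii): "ii) an increase of ≥2 points on one of the appropriate Functional System Scores (FSS")
- limb (iii): "an increase of >1 point on two or more of the appropriate FSS"

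The limbs are joined by or, so any one is enough. Limbs (i) and (ii) use an at-least sign; limb (iii) uses a strict greater-than sign.

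The Clinical evaluation section says that the EDSS "measures impairments in eight functional systems, including vision, brainstem, pyramidal, cerebellar, sensory, bowel and bladder, mental (cerebral) and ambulation". It does not give the step size of the individual system scores. The only half-point step in the article concerns the total EDSS, in the progression criterion for patients with a baseline score of 5.5 to 6.5. The article contains no second relapse definition.

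**The concern.** A third alternative in such a definition should catch something that the first two miss. The natural role for a limb about two or more systems is to catch milder change spread over several systems, where no single system moves by 2 points and the total score moves little. With the strict sign, limb (iii) asks for at least as much per system as limb (ii), and asks for it in more systems. It can then never be the deciding criterion.

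Relapses belong to the primary safety assessment. Each cohort has 3 to 5 patients and each trial 9 to 15, so one reclassified event is visible in the report. The article also relies on harmonised clinical evaluation to compare the two routes of administration. If one site applies the strict sign literally and the other reads it as at least 1, their relapse counts do not measure the same thing.

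**Working it through.** This is a check of a logical rule; there is no figure in the plan to reproduce.

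**Inputs.** The three limbs and their or-combination come from the Safety section, and the eight functional systems from Clinical evaluation. Two inputs are assumptions: FSS change in whole points, and one system in limb (ii) means at least one system.

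**Step 1: logic.** Let d be the rise in a system since the previous assessment. For whole numbers, d > 1 is the same as d ≥ 2. Limb (iii) is then d ≥ 2 in at least two systems, which is contained in d ≥ 2 in at least one system, that is, in limb (ii).

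**Step 2: enumeration.** Let each system rise by 0, 1, 2 or 3 points.

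| Systems | Patterns | Meet (iii) as written but not (ii) | Would meet (iii) read as ≥1 but not (ii) |
|---|---|---|---|
| 8 (as listed in the article) | 4^8 = 65,536 | 0 | 2^8 − 1 − 8 = 247 |
| 7 (sensitivity check) | 4^7 = 16,384 | 0 | 2^7 − 1 − 7 = 120 |

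The last column counts patterns made up only of 0s and 1s, less the pattern with no rise and those with a single rise. These are exactly the 1-point rises in two or more systems. They are counts of patterns, not frequencies in patients.

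**Step 3: limb (i).** Take a 1-point rise in two systems and none elsewhere, and vary the rise in total EDSS.

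| Rise in total EDSS | Relapse as written | Relapse if (iii) read ≥1 |
|---|---|---|
| 0 | no | yes |
| 0.5 | no | yes |
| 1.0 | yes, by (i) | yes |
| 1.5 | yes, by (i) | yes |

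The sign therefore matters only when the total rises by less than 1.

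**Step 4: dependence on the assumptions.**

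- Half-point FSS steps (rises of 0 to 2 points, 7 systems, 5^7 = 78,125 patterns): limb (iii) as written would add 4^7 − 3^7 − 7 × 3^6 = 16,384 − 2,187 − 5,103 = 9,094 patterns. The redundancy thus needs whole-point scoring. A rise of exactly 1 point in several systems would still fail both FSS limbs.
- If limb (ii) meant exactly one system, limb (iii) would no longer be redundant. With whole points, however, (ii) and (iii) together would still cover only patterns with a rise of at least 2 somewhere, so 1-point rises in several systems would stay outside both.

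**The case against.** Four points can be made on the other side.

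- **Whole-point scoring is not in the article.** Correct, so the redundancy is conditional on it. The exclusion of rises of exactly 1 point from both FSS limbs does not depend on it.
- **Limb (i) compensates.** In part. A reader might infer that relapses with 1-point rises in several systems are never counted. The document does not support that: the limbs are alternatives, and such an event counts whenever the total EDSS rises by at least 1. The gap is limited to total rises of 0 or 0.5. It is not closed, because limb (i) asks for 1 point at every EDSS level, including 5.5 to 6.5, where the progression criterion accepts a sustained 0.5.
- **The safety signal is not lost.** A reader might infer that safety events go uncounted. The document does not show this. The primary safety objective is the occurrence and severity of adverse events; Table 4 has them recorded continuously; and MRI monitors disease activity independently of the relapse definition. What may change is the label. The escalation rule rests on dose-limiting toxicities and on the judgement of the investigators and the DSMB, not on relapse counts, and the Analysis section plans no confirmatory testing.
- **No number of missed relapses can be stated.** One could assume 0.5 relapses per patient-year and that 20 to 40% of relapses would qualify only through a limb (iii) read as at least 1. Follow-up from V1 to F12 is about 14 + 52 = 66 weeks. Nine patients would then have 9 × 66/52 × 0.5 = 5.7 relapses and fifteen 9.5, of which 1.1 to 3.8 would be missed across that range. Neither the rate nor the share has any basis in the article, so this is only a scenario and carries no weight in the conclusion.

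A reading error in the PDF is unlikely, since the at-least sign survives twice in the same sentence.

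**Conclusion.** The definition does not work as written. Under whole-point FSS, and with limb (ii) read as at least one system, limb (iii) is a subset of limb (ii) and adds no case. A 1-point rise in two or more systems is classed as a relapse only if the total EDSS also rises by at least 1; otherwise it is not labelled a relapse, though it can still be recorded as an adverse event.

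Reading the third limb as at least 1 point is the evident way to give it a role. The strict sign beside two at-least signs suggests a slip, but the article does not confirm it.

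Severity is moderate to minor. It concerns an outcome definition within the primary safety assessment and the comparability of two very small trials, but no decision rule depends on it.

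**What to change.** 1. Check limb (iii) in both full protocols and reconcile its sign with limb (ii), so that the third limb has a function. At least 1 point appears to be intended; the sponsor should confirm this before the text is changed.
2. State the FSS step size, and that limb (ii) means at least one system.
3. Confirm that both trials use the same wording.
4. Only if the strict sign was applied literally, reclassify recorded events from the stored FSS at the event and at the previous assessment. The article does not say that individual system scores are kept, so this should be checked first.

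The cost is a one-sign correction and, if step 4 applies, a review of records from at most 2 × 15 = 30 evaluable patients. The downside is that slightly more events would be labelled relapses. The article also mentions discretionary steroid treatment in case of relapse; this point concerns outcome classification only and takes no position on treatment.
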